# TREATMENT PLAN

## Agent Administration

Treatment will be administered either on an outpatient basis or remotely, as a telemedicine visit. Reported adverse events and potential risks are described in Section 7. Appropriate dose modifications are described in Section 6. No investigational or commercial agents or therapies other than those described below may be administered with the intent to treat the patient’s disease process.

| **Dose Escalation Design** | | | | |
| --- | --- | --- | --- | --- |
| **Cohort** | **Dose (mg)** | **Number of Treatment Cycles** | **Designated Weeks of Artesunate Administration** | **Number Subjects** |
| **I** | 200 | 2 | 0, 2 | 3 |
| **II** | 200 | 3 | 0, 2, 4 | 3 |
| **III** | 400 | 2 | 0, 2 | 3 |
| **IV** | 400 | 3 | 0, 2, 4 | 3 |
| **V** | 600 | 2 | 0, 2 | 3 |
| **VI** | 600 | 3 | 0, 2, 4 | 3 |

***Note: Each cycle = 5 days

Artesunate suppositories will be administered intra-anally on days 1 to 5, and the dosing schedules will vary between 2 and 3 cycles. A dose-limiting toxicity for the Artesunate suppository is defined as any Grade 2 or greater toxicities in any organ system (or Grade 3 or greater toxicities), as delineated in CTCv4.0. Patients will be continued on treatment until disease progression to cancer, unacceptable toxicity, death, pregnancy, withdrawal of consent, or study termination.

The MTD will be determined utilizing a modified 3 + 3 design. The 3 + 3 dose escalation will consist of 6 dose levels in combination with variation in dosing schedules the single agent Artesunate, with additional de-escalation steps. An expansion cohort of 12 patients will be included at the MTD. Once MTD is found, then secondary outcomes will be evaluated.

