## Definition of Dose-Limiting Toxicity

A dose-limiting toxicity (DLT) is defined as any drug-related Grade 2 (moderate; minimal, local, or noninvasive intervention indicated; limiting age appropriate instrumental ADL) or greater drug-related toxicities in any organ system (or Grade 3 or greater toxicities–severe or medically significant but not immediately life-threatening; hospitalization or prolongation of hospitalization indicated; disabling; limiting self care ADL**) in any organ system (including gastrointestinal, dermatologic, and neurologic), as delineated in Common Terminology Criteria for Adverse Events v4.0 (CTCAE).

This above definition of dose-limiting toxicity applies to the drug that is being studied—the artesunate suppository. Post-procedural complications related to the HRA procedure are not dose limiting.

The dose limiting toxicity determining period for the study will extend to 1 week after the last cycle of artesunate suppository. Thus, for the 2 cycles, the DLT determining period will extend to 3 weeks; for 3 cycles, it will extend to 5 weeks.

Beyond the DLT determining period, if patients in a specific cohort have complete resolution of their high-grade dysplastic lesions, then the plan will be to stop at this dosing cycle and frequency and move into the 12-patient expansion cohort.

Management and dose modifications associated with the above adverse events are outlined in Section 6.

Dose escalation will proceed within each cohort according to the modified 3+ 3 design with de-escalation schema and an expansion cohort at MTD. Dose-limiting toxicity (DLT) is defined as above.

The specific details are as follows,

The 3 + 3 dose escalation will consist of 6 dose levels in combination with variation in dosing schedules the single agent Artesunate, with additional de-escalation steps. An expansion cohort of 12 patients will be included at the MTD. Once MTD is found, then secondary outcomes will be evaluated. In MTD expanded patient cohort, anal intraepithelial neoplasia (AIN) regression from AIN 2/3 to low-grade anal intraepithelial neoplasia (AIN 1) or no residual AIN will be assessed through subsequent HRA evaluation. Cytology specimens will be tested through quantitative PCR for HPV viral load during initial and subsequent HRA evaluations. A tissue bank will be created for future studies.

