# ADVERSE EVENTS: LIST AND REPORTING REQUIREMENTS

Because this is a pilot study evaluating tolerability of a new intra-anal treatment, the stopping rule for safety is the presence of drug-related Grade 3 toxicity in any organ system (including gastrointestinal, dermatologic, and neurologic toxicities) delineated in CTCAEv4.0. In the event of two identical unexpected treatment-related Grade 2 or greater toxicities in any organ system ( or other Grade 3 or greater toxicities), accrual will be suspended pending further review.

Subjects who become pregnant during study will be required to discontinue drug. Although not considered an adverse event, pregnancy will be reported in the same way. Whenever possible, a pregnancy should be followed to term, and the status of mother and child reported. The Pregnancy Notification form will be sent to the principal investigator ([name]) within 48 hours of discovery. Whenever possible, the Follow-up Pregnancy Outcome Form will be filled after delivery.

Finally, if there is evidence of disease progression at the interval visit regardless whether the progression may or may not be associated with Artesunate, patients will undergo HRA biopsy and ablation at that point.

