## Dosage and Administration

the first dosing visit (week 0) will be an in-person visit, in which tthe study physician or nurse will administer the first of five daily intra-anal suppositories for each enrolled subject at the study site. The subjects will be trained by the physician or nurse on the insertion of artesunate suppositories transanally during that visit, and instructed to administer four subsequent daily doses at home. All subsequent dosing visits (weeks 2 and 4) will be performed as telemedicine visits. For telemedicine visits, the physicians will review the symptom diaries and patients will be instructed about suppository administration over the phone. Within 5 days of the last day of the cycle(s), patients will receive a telephone call to assess for any AE. If patients do not experience any symptoms or AEs after suppository administration, then the subsequent dosing visits will be telemedicine visits. However, if patients experience AEs, then the subsequent dosing visits will be in-person visits, at which time the physician will perform an anoscopy.

The first 3 study subjects (healthy volunteers with AIN2/3) will receive five (5) daily suppositories that contain 200 mg Artesunate for a total of 2 cycles at weeks 0 and 2. The 200 mg dose (or ≤ 4 mg/kg for subjects weighing 50 kg at minimum) is considerably lower than that used when the anal suppository is intended to deliver a systemic dose of drug for malaria – the 10 mg/kg (50 mg) suppository is recommended by WHO for pediatric care. If no severe local irritation or systemic toxicities are observed in the first 3 patients at 200 mg, the dosage will escalate to 3 cycles of 200 mg per day. Doses of escalation will be 200 mg, 400 mg, and 600 mg. Suppositories will be administered daily for 5 days. Five days constitutes 1 cycle. Up to 3 cycles will be administered at Weeks 0, 2, and 4. Please see section 5 for dose escalation schema.

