# STATISTICAL CONSIDERATIONS

## Study Design/Endpoints

The primary objective of this trial is to determine the MTD or recommended Phase 2 dose (RP2D) of Artesunate. The MTD will be determined using a modified 3 + 3 design, in which the MTD is defined as the highest dose level tested at which ≤20% patients experience dose limiting toxicity (DLT). The 3 + 3 dose escalation will consist of 6 dose levels in combination with variation in dosing schedules the single agent Artesunate. In addition, if DLT’s are identified at any dose, there are possible intermediate dose de-escalation steps allowed (i.e. to have only one administration at a particular dose) An expansion cohort will occur at MTD. Once MTD is found, then secondary outcomes will be evaluated. There is a 1-week washout period before advancing to the next Artesunate dose level.

| **Dose Escalation Design** | | | | |
| --- | --- | --- | --- | --- |
| **Cohort** | **Dose (mg)** | **Number of Treatment Cycles** | **Designated Weeks of Artesunate Administration** | **Number of patients** |
| **I** | 200 | 2 | 0, 2 | 3 |
| **II** | 200 | 3 | 0, 2, 4 | 3 |
| **III** | 400 | 2 | 0, 2 | 3 |
| **IV** | 400 | 3 | 0, 2, 4 | 3 |
| **V** | 600 | 2 | 0, 2 | 3 |
| **VI** | 600 | 3 | 0, 2, 4 | 3 |

More specifically:

This is a modified 3 + 3 design. Based on previous studies of rectally administered Artesunate for the treatment of malaria, the safety profile demonstrates a low probability of dose limiting toxicity in children, as well as adults. The first cohort will consist of 3 patients who receive the initial dose of a 200-mg suppository administered in cycles of 5 daily doses at weeks 0 and 2. If none of the three patients in a cohort experiences a dose-limiting toxicity, another three patients will be treated at the next higher dose level. If 1 out of 3 patients experiences dose-limiting toxicity, then the next 3 patients will be treated at the same dose level. If 2 out of 6 patients experience a DLT, then de-escalation to the next lower level will occur. The modification of the 3 + 3 design consists of the extra de-escalation steps as noted on the left of the diagram pictured below.

If any dose has 2 (or more) DLTs then the MTD will be the dose that is below that dose that has 1 or less DLTs out of 6 patients. Once the MTD is identified then additional patients will be added to this cohort to allow a total of 12 patients.

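### Sections 5.1 and 5.2 cite dose modifications that Section 6 does not contain; separately, 14.1 and 11.1 do not keep patients who took only part of the regimen out of the escalation count

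*Protocol*

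**What the plan says.** **Dose modifications.** Section 5.1 (Agent Administration) states: "Appropriate dose modifications are described in Section 6". Section 5.2 (Definition of Dose-Limiting Toxicity) repeats this for the DLT events: "Management and dose modifications associated with the above adverse events are outlined in Section 6".

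**Escalation.** Section 14.1 states: "If none of the three patients in a cohort experiences a dose-limiting toxicity, another three patients will be treated at the next higher dose level". One DLT in three adds three patients at the same level. Two or more DLTs put the MTD at a lower level with at most one DLT in six. No number of doses or cycles, and no completed follow-up, is required of the patients counted. The word evaluable appears only in the accrual sentence of 14.2, undefined.

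**Dose levels.** Levels I and II, III and IV, and V and VI share a dose and differ only in having two or three cycles.

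**DLT period.** Under 5.2 it ends one week after the last cycle: 3 weeks for two cycles, 5 weeks for three.

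**Replacement.** Section 11.1 defines a dropout by failure to return for at least week 16, and replaces dropouts.

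**Exposure.** Section 5.3 foresees delays for adverse events and stops for intercurrent illness, unacceptable events, patient decision or investigator judgment. Under 6.9 the first dose is given on site and patients are "instructed to administer four subsequent daily doses at home". Section 6.11, headed as a compliance assessment, sets no compliance criterion. The diary in Appendix B has a daily column for whether the suppository was taken.

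**The concern.** There are two separate problems. The first is documentary: two sections rely on text that is not there, so two sites have no written dose-modification rule to follow.

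The second bears on the primary result. Cycle number is part of what defines a level, so a patient who took one of three cycles has not tested that level. If such patients stay in the count and DLT risk accumulates over cycles, the observed DLT rate of the named level is biased downward. A level could then be cleared, or named as the MTD, partly on a regimen that was not taken. The replacement rule does not prevent this, because it looks at the week 16 visit and not at exposure or the DLT period.

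**Working it through.** **1. What Section 6 contains**

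| Topic | What is there |
|---|---|
| Trial-level stopping | "the stopping rule for safety is the presence of drug-related Grade 3 toxicity in any organ system" |
| Accrual | After two identical unexpected related toxicities of Grade 2 or more, or other Grade 3 or more: "accrual will be suspended pending further review" |
| Discontinuation in one patient | "Subjects who become pregnant during study will be required to discontinue drug" |
| Progression | Biopsy and ablation |
| 6.1 to 6.4 | Seriousness, attribution, reporting |
| 6.5 to 6.11 | Formulation, supply, administration, diary review |
| 6.9 on escalation | Refers back: "Please see section 5 for dose escalation schema" |

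None of these modifies a patient's dose or cycle after an adverse event. The table of contents lists 6.1 to 6.11 and none has that title. Section 5.1 also sends the reader to Section 7 for adverse events, but Section 7 covers biomarkers. That pattern fits section numbers that were not updated.

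**2. The stated rules applied to two patients at a three-cycle level**

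- Patient A takes cycle 1, stops for a Grade 1 event, has no DLT and attends week 16. Section 14.1 does not exclude A, and 11.1 does not call A a dropout. A stays in the count.
- Patient B takes all three cycles, is followed through the 5-week DLT period without a DLT, and misses week 16. B is a dropout and is replaced, although B is fully informative for escalation.

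Week 16 falls 16 − 5 = 11 weeks after the DLT period ends for three cycles, and 16 − 3 = 13 weeks after it for two. If escalation follows the DLT period, dropout status is not yet known when the decision is taken.

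**3. Doses away from the site**

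Two cycles are 2 × 5 = 10 doses; three are 3 × 5 = 15. If weeks 2 and 4 are telemedicine visits, 1 of 10 or 1 of 15 doses is given on site.

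**4. Illustration of size**

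From 14.1, a level is cleared by 0/3, or by 1/3 followed by 0/3:

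P(clear) = P0 + P1 × P0.

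Assumptions not in the protocol: the true full-regimen DLT risk p; equal risk per cycle, so that the one-cycle risk of a K-cycle regimen is q = 1 − (1 − p)^(1/K); and one patient in each three receiving only cycle 1.

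- Full dosing: P0 = (1 − p)³, P1 = 3p(1 − p)².
- One early stop per three: P0 = (1 − p)²(1 − q), P1 = 2p(1 − p)(1 − q) + (1 − p)²q.

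For K = 3 and p = 0.40, q = 1 − 0.6^(1/3) = 0.157.

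- Full: 0.216 + 0.432 × 0.216 = 0.309.
- One early stop per three: P0 = 0.36 × 0.843 = 0.304; P1 = 0.405 + 0.056 = 0.461; P(clear) = 0.304 + 0.461 × 0.304 = 0.444.

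| Level | True risk p | Full dosing | One in three stops after cycle 1 |
|---|---|---|---|
| 3 cycles | 0.20 | 0.709 | 0.798 |
| 3 cycles | 0.33 | 0.434 | 0.567 |
| 3 cycles | 0.40 | 0.309 | 0.444 |
| 2 cycles | 0.33 | 0.434 | 0.530 |
| 2 cycles | 0.40 | 0.309 | 0.405 |

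The timing of risk matters. At p = 0.40, if all risk lies in cycle 1, then q = p and the probability stays at 0.309. If all risk lies after cycle 1, then q = 0 and it is 0.36 + 0.48 × 0.36 = 0.533.

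**5. Sample size, for the cost of replacement**

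The expected 36 in 14.2 is 6 levels × 6 patients. One way to reach 60 is 36 + 3 one-cycle de-escalation levels × 6 + 6 to bring the MTD cohort to 12, so 36 + 18 + 6 = 60. The protocol does not show this sum. Twelve new expansion patients in place of 6 would give 66.

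**The case against.** The strongest reply is that 14.1 is silent. A reader might infer that it counts partly treated patients as DLT-free, but it states no such rule. A separate analysis plan, not shown here, could define an evaluable set. The silence is conceded. The point still stands, because the protocol itself fixes both the escalation count and the replacement rule. These operate during the trial, and applied as written they keep patient A and replace patient B.

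The exposed group is also narrow. Under 5.2 any drug-related event of Grade 2 or more is a DLT, so a patient who stops for one already counts against the level. A patient with a DLT in cycle 1 is counted whether or not cycle 2 follows, so the missing dose-modification text does not itself create the bias. What remains are stops for Grade 1 or unrelated events, illness, missed doses, or patient or investigator decision. This limits the size and does not close the gap.

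Home dosing does not show poor adherence. Section 6.9 provides calls after each cycle and makes later dosing visits in person when a patient has had adverse events; diaries are reviewed. That is fair, but none of it is linked to who is counted.

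A reader might also infer that tolerability is never summarised. That is not so: 14.3 tabulates the maximum toxicity grade per patient by category, grade and dose level. What is not stated is how much of the assigned regimen was taken.

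**Conclusion.** The reference error is certain: 5.1 and 5.2 point to dose modifications that Section 6 does not hold, and the passages must be reconciled.

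The escalation gap is real but limited. The protocol sets no exposure or follow-up condition for the count, and ties replacement to a visit 11 to 13 weeks after the DLT period. The direction of the bias needs only that DLT risk accumulates with cycles. Its size cannot be taken from the documents. The rise from 0.31 to 0.44 rests on an assumed 40% risk, equal risk per cycle and one early stop in each three patients; under other timing of risk the second figure runs from 0.31 to 0.53. It shows what the gap could do and does not forecast how often patients will stop.

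One might go further and count anyone who stops for a drug-related event against the level. The documents do not support that: it would change the Grade 2 threshold in 5.2, which is a clinical definition.

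**What to change.** 1. Reconcile 5.1 and 5.2 with Section 6: insert the text intended there, or remove the references. The content is for the sponsor's physicians.
2. In 14.1, define a DLT-evaluable patient as one who had a DLT, or who took at least a pre-stated share of the assigned suppositories and was followed through the DLT period in 5.2. A share of 80% would serve as an example: 8 of 10 or 12 of 15. It is an analysis threshold, not a dosing rule.
3. Replace non-evaluable patients for the escalation decision. Align 11.1 by tying replacement for that decision to DLT evaluability, not to week 16.
4. Report by level the share of assigned suppositories taken, and the number of patients stopped or replaced with reasons. Replacing patients who stopped for drug-related events below the DLT threshold could favour tolerant patients, so this must be visible. The DLT definition is unchanged.

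The cost is a few sentences, one table and an occasional replacement patient. Replacements should be checked against the cap of 60, which the sum shown above already uses in full. Exposure data come from the diary but will be incomplete for some patients, because Appendix B tells those who miss more than two days of entries not to fill them in. The rule should say how missing entries are treated.

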## Duration of Therapy

In the absence of treatment delays due to adverse event(s), treatment may continue for the 40-week research study period or until one of the following criteria applies:

- Disease progression to cancer
- Intercurrent illness that prevents further administration of treatment
- Unacceptable adverse event(s)Patient decides to withdraw from the study
- General or specific changes in the patient’s condition render the patient unacceptable for further treatment in the judgment of the investigator.

## Duration of Follow Up

Patients will be followed for a total of 40 weeks from the first day of administration of the study drug or until death, whichever occurs first. Patients removed from study treatment for unacceptable adverse event(s) will be followed until resolution or stabilization of the adverse event.

Please see the schematic diagram for treatment follow-up as outlined in the Protocol Synopsis section.

## Criteria for Removal from Study Treatment

Patients will be removed from study treatment when any of the criteria listed in Section 5.3 applies. The reason for study removal and the date the patient was removed must be documented in the Case Report Form.

#

# ADVERSE EVENTS: LIST AND REPORTING REQUIREMENTS

Because this is a pilot study evaluating tolerability of a new intra-anal treatment, the stopping rule for safety is the presence of drug-related Grade 3 toxicity in any organ system (including gastrointestinal, dermatologic, and neurologic toxicities) delineated in CTCAEv4.0. In the event of two identical unexpected treatment-related Grade 2 or greater toxicities in any organ system ( or other Grade 3 or greater toxicities), accrual will be suspended pending further review.

Subjects who become pregnant during study will be required to discontinue drug. Although not considered an adverse event, pregnancy will be reported in the same way. Whenever possible, a pregnancy should be followed to term, and the status of mother and child reported. The Pregnancy Notification form will be sent to the principal investigator ([name]) within 48 hours of discovery. Whenever possible, the Follow-up Pregnancy Outcome Form will be filled after delivery.

Finally, if there is evidence of disease progression at the interval visit regardless whether the progression may or may not be associated with Artesunate, patients will undergo HRA biopsy and ablation at that point.

## Definition of a Serious Adverse Event

A serious adverse event or reaction is any untoward medical occurrence that at any dose:

- - - results in death
    - is life-threatening (an event in which the subject is at risk of death at the time of the event; it does not refer to an event which hypothetically might have caused death if it were more serious)
    - requires inpatient hospitalization or prolongation of existing hospitalization
    - results in persistent or significant disability or incapacity
    - is a birth defect/congenital anomaly

## Adverse Event Characteristics

- **CTCAE term (AE description) and grade:** The descriptions and grading scales found in the revised NCI Common Terminology Criteria for Adverse Events (CTCAE) version 4.0 will be utilized for AE reporting. All appropriate treatment areas should have access to a copy of the CTCAE version 4.0. A copy of the CTCAE version 4.0 can be downloaded from the CTEP web site <http://ctep.cancer.gov/protocolDevelopment/electronic_applications/ctc.htm>.
- **Attribution** of the AE:
  - Definite – The AE *is clearly related* to the study treatment.
  - Probable – The AE *is likely related* to the study treatment.
  - Possible – The AE *may be related* to the study treatment.
  - Unlikely – The AE *is doubtfully related* to the study treatment.
  - Unrelated – The AE *is clearly NOT related* to the study treatment.

## Expedited Adverse Event Reporting

The severity of each adverse event must be assessed using the NCI Common Terminology Criteria for Adverse Events, v4.0 (CTCAE 4.0).

All adverse events that occur from the time of study drug administration through 30 days after the final treatment will be recorded. Duration, severity, treatments administered and outcome for each adverse event will be recorded on the CRF (case report form) for the following visit. Drug related adverse events will be followed until resolved, until no further improvement is expected, until a non-study antitumor therapy is initiated, or for 30 days after last study treatment, whichever comes first (with the exception of neuropathy, which must be followed until resolution to toxicity grade 1 or until stable for 60 days).

Adverse events beginning 30 days after the last treatment that the investigator considers to be related to study treatment will be reported to the appropriate contact person at any time such events occur.

Conditions that were present at the study start and that worsen during the study should be reported as beginning on the date the event worsened, not the date it began pre-study. Event text may include the word “worsened” or “exacerbated.”

Conditions which were recorded as “intermittent” at the study start which occur during the study must be reported if they are more frequent or of greater severity.

**Phase 1 and Early Phase 2 Studies: Expedited Reporting Requirements for Adverse Events that Occur on Studies under an IND/IDE within 30 Days of the Last Administration of the Investigational Agent/Intervention** 1, 2

| **FDA REPORTING REQUIREMENTS FOR SERIOUS ADVERSE EVENTS (21 CFR Part 312)**  **NOTE:** Investigators **MUST** immediately report to the sponsor (NCI) **ANY** Serious Adverse Events, whether or not they are considered related to the investigational agent(s)/intervention (21 CFR 312.64)  An adverse event is considered serious if it results in **ANY** of the following outcomes:   1. Death 2. A life-threatening adverse event 3. An adverse event that results in inpatient hospitalization or prolongation of existing hospitalization for ≥ 24 hours 4. A persistent or significant incapacity or substantial disruption of the ability to conduct normal life functions 5. A congenital anomaly/birth defect. 6. Important Medical Events (IME) that may not result in death, be life threatening, or require hospitalization may be considered serious when, based upon medical judgment, they may jeopardize the patient or subject and may require medical or surgical intervention to prevent one of the outcomes listed in this definition. (FDA, 21 CFR 312.32; ICH E2A and ICH E6). | | |
| --- | --- | --- |
| **ALL SERIOUS** adverse events that meet the above criteria MUST be immediately reported to the NCI via electronic submission within the timeframes detailed in the table below. | | |
| **Hospitalization** | **Grade 3-5**  **Timeframes** |  |
| Resulting in Hospitalization  ≥ 24 hrs | 24-Hour 5 Calendar Days |  |
| Not resulting in Hospitalization  ≥ 24 hrs |  |
| **NOTE:** Protocol specific exceptions to expedited reporting of serious adverse events are found in the Specific Protocol Exceptions to Expedited Reporting (SPEER) portion of the CAEPR.  **Expedited AE reporting timelines are defined as:**   - “24-Hour; 5 Calendar Days” – The AE must initially be submitted electronically within 24 hours of learning of the AE, followed by a complete expedited report within 5 calendar days of the initial 24-hour report. | | |
| 1Serious adverse events that occur more than 30 days after the last administration of investigational agent/intervention and have an attribution of possible, probable, or definite require reporting as follows:  **Expedited 24-hour notification followed by complete report within 5 calendar days for:**   - All Grade 3, 4, and Grade 5 Aes | | |

